### 10.3.3 Secondary Analyses

In addition to the primary endpoint, all secondary endpoints listed in chapter 6.3 will be evaluated and tested for differences between interventional and standard treatment. The obtained p-values will be interpreted in a strictly exploratory fashion only, and no correction for multiple comparisons will therefore be applied. Statistical analyses for (secondary and exploratory) endpoints measured at multiple timepoints will focus on repeated measure models, to address the dependencies between visits. This will be a Generalized Estimating Equation model in case of binary data, and a mixed-effects model in case of continuous data. If data are not fulfilling underlying model assumptions, a transformation may be necessary before applying the statistical model. Details will be described in the SAP.

### 10.3.4 First Secondary Analyses – Epithelialization at Visit 8

The percentage of epithelialization of a site is the percentage of the grafted area which is closed/healed with dry epithelium, as noted in chapter 8.2.

### 10.3.5 Secondary Analyses - Clinical and Microbiological Signs of Infection at Visits 4 and 5:

At each of the 2 visits, infections which can be linked to one of the two sites will determine for each patient whether an infection occurred on either site.

Infections which cannot be linked to a site will be listed.

### **10.3.6 Secondary Analyses – Scar Quality (Elasticity of the Study Areas at Visit 10 (Cutometer®))**

The Cutometer® parameters (ratio of study site versus matching normal skin for both study areas) used to assess elasticity will be analysed comparing the difference between the 2 study areas. The estimate for the treatment difference will be provided with its 95% confidence interval.

### **10.3.7 Secondary Analyses – Scar Quality (General Quality at Visit 10 (POSAS))**

The 6 patient variables, the patient overall opinion, the 6 observer parameters, their sum and the observer overall opinion will be analysed. 8.2.4.

### **10.3.8 Secondary Analyses – AE Reporting (during full study duration)**

All adverse events will be listed by patient, phase (pre-treatment, treatment, post-treatment) and date of onset.

Adverse events with an onset date during the treatment phase will be summarized in a frequency table. Adverse events with an onset date during the pre-treatment phase or the post-treatment phase will be summarized the same way.

If appropriate, additional tables will be prepared for selected adverse events (e.g.: adverse event leading to treatment discontinuation, serious adverse events).

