### 6.3 Secondary Endpoints

Safety and efficacy evaluation, as a comparison between the EHSG-KF and control sites, based on:

- Main secondary safety endpoint:
  - Clinical and microbiologic signs of infection at visits 4 (6-10 days post grafting) and 5 ( $21 \pm 2$  days post grafting)
- Main secondary efficacy endpoints: Scar quality at the study areas
  - Assessment of elasticity of the study areas using the Cutometer® at visit 10 (1 year  $\pm 30$  days post grafting)
  - Assessment of general scar quality at the study areas using the POSAS, a reliable and validated scar assessment tool, at visit 10 (1 year  $\pm 30$  days post grafting)
- Other secondary safety endpoint:
  - Assessment and reporting of all observed adverse events will be carried out for the full duration of the study from visit 2 on
- Other secondary efficacy endpoint:
  - Epithelialization at visit 6 ( $28 \pm 3$  days post grafting)

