## **9.2 Recording of Adverse Events and Other Safety Related Events**

Investigators and ultimately the PI have the primary responsibility for AE identification, documentation, and assessment i.e., with regard to seriousness, severity grading, and relatedness to the investigational intervention. This responsibility is applicable during the entire study period, regardless of the relation to the IMP.

Study patients will be instructed to report all AEs and will be routinely questioned about AEs at study visit 2 to visit 12 if possible. The well-being of the patients will be ascertained by neutral questioning (“How are you?”). All AEs will be followed until the event (or its sequelae) resolves or stabilizes at a level acceptable to the Investigators.

All observed or volunteered AEs will be fully documented in the patient file and subsequently recorded in the eCRF. For each AE, the information to be recorded in the source document and in the eCRF includes the nature of the AE, date and time of onset, seriousness, severity, causality (relationship to study product), duration, action taken and outcome of the event.

For all AEs, sufficient information will be pursued and/or obtained so as to permit an adequate determination of the outcome of the event (i.e., whether the event should be classified as a SAE) and an assessment of the causal relationship between the AE and the investigational study treatment. Even if the AE/SAE is assessed by the Investigator as not reasonably related to study product, its occurrence must be recorded in the source documents and in the eCRF. If an AE becomes a SAE, the corresponding eCRF entries are created.

Lack of efficacy per se will not be reported as an AE. The signs and symptoms or clinical sequelae resulting from lack of efficacy will be reported as an AE or SAE if they fulfil the AE or SAE definitions (including clarifications).

All AEs are reported in standardized terminology according to MedDRA adverse event coding dictionary version 18.1. Whenever available, the underlying disease or condition for which a therapeutic or diagnostic procedure is required should be reported as the AE term.

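### Adverse events are promised as a comparison between the two graft areas, but the protocol neither requires the area to be recorded nor tabulates by it

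*Protocol*

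**What the plan says.** Section 6.3 of the protocol introduces the secondary endpoints as "Safety and efficacy evaluation, as a comparison between the EHSG-KF and control sites, based on" a list that includes, as a further safety item, "Assessment and reporting of all observed adverse events will be carried out for the full duration of the study from visit 2 on". Section 10.3.3 says that "all secondary endpoints listed in chapter 6.3 will be evaluated and tested for differences between interventional and standard treatment". Neither section exempts AEs.

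Section 9.2 sets out what is recorded for each AE: "nature of the AE, date and time of onset, seriousness, severity, causality (relationship to study product), duration, action taken and outcome of the event". Section 9.2.1 adds that certain recurring symptoms in the treatment phase, among them pruritus, pain and granulation tissue, are entered once with a first and a last date.

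The analysis in section 10.3.8 is: "All adverse events will be listed by patient, phase (pre-treatment, treatment, post-treatment) and date of onset". It continues: "Adverse events with an onset date during the treatment phase will be summarized in a frequency table", and events of the other two phases are handled the same way. Study area appears in neither the listing nor the tables.

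Section 10.3.5 handles the infection endpoint differently. There, "infections which can be linked to one of the two sites" are assigned to that site, and those that cannot be linked are listed.

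**The concern.** In a design with parallel groups, an AE table by patient becomes a treatment comparison once it is split by arm. Here each patient is his or her own control: section 3.3 places EHSG-KF on one area and meshed STSG on the other in the same operation. Treatment is a property of the area, not of the patient. An AE can contribute to a comparison only if it is tied to an area, and the protocol does not require that tie outside the infection endpoint.

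At stake is what the trial can say about local safety. Section 9.7 expects the complications of grafting to be largely local. For those with no per-area endpoint of their own, the planned output would show how often they occurred in the trial but not on which graft.

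**Working it through.** The protocol gives no figure for this point, so the main check sets its sections against each other.

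1. **What is promised.** Section 2.3 lists AE reporting under an objective framed as a comparison with meshed STSG. Section 6.3 repeats that frame, and 10.3.3 promises a test for every 6.3 endpoint. Section 10.2 also says that all secondary endpoints will be tested, in an exploratory way.
2. **What is collected.** The items listed in 9.2 do not include location or study area. Under 9.2.1, granulation tissue on one area and granulation tissue on both can give the same single entry.
3. **What is tabulated.** Section 10.3.8 uses patient, phase and onset date. Section 10.3.1 analyses safety as treated, but every patient is treated with both grafts, so that rule creates no groups to compare.
4. **Whether relatedness can stand in.** Section 9.3.1 asks for relationship to the study procedures or the investigational product. STSG grafting is a study procedure (section 5.3), so an event on the control area can be judged procedure-related. So can an event on the EHSG-KF area. The flag does not separate the areas.
5. **What the protocol does in like cases.** Section 10.3.10 makes quality of life and resource use purely descriptive because they belong to the patient rather than the site. Section 10.3.5 links infections to a site. AEs receive neither treatment.

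**What a per-patient count hides (hypothetical, for scale).** Suppose 6 of 12 patients have a local AE on exactly one area:

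| EHSG-KF area | Control area | Difference in proportions | Planned table shows |
|---|---|---|---|
| 6 | 0 | 6/12 − 0/12 = +0.50 | 6 of 12 |
| 3 | 3 | 3/12 − 3/12 = 0 | 6 of 12 |
| 0 | 6 | 0/12 − 6/12 = −0.50 | 6 of 12 |

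**What recording the area could deliver.** In an exact McNemar test with m discordant patients, all in one direction, the two-sided p is 2 × 0.5^m:

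- m = 5: 2 × 0.03125 = 0.0625
- m = 6: 2 × 0.015625 = 0.031

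So at least six discordant patients, all in one direction, are needed for p < 0.05. That is half of 12 patients (6/12), or 40% of 15 (6/15).

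**The case against.** The strongest reply has four parts.

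- **The area may in fact be recorded.** Section 9.2 says the recorded information includes the listed items, so the list is not closed. The nature of the AE may name a location, and the eCRF design sits in documents not shown here. This stands in part: a reader might infer that the area is not recorded at all, and the protocol does not show that. It shows only that the area is not required.
- **Table layout belongs to the SAP.** Section 10.3.3 leaves details to it, and 10.3.8 allows extra tables for selected events. This is true of layout. But an SAP cannot split events by an attribute that sites were not required to collect, and the present text promises a comparison in one section and plans none in another.
- **Local outcomes are already measured per area.** This stands for graft take (8.2.2), epithelialization and wound closure (8.2.1), scar quality (8.2.3 to 8.2.6) and infection (8.2.7, 10.3.5). A reader might infer that the trial cannot compare graft loss or scarring; the documents do not support that. Pain and itching are also POSAS patient items, but only from visit 8.
- **The comparison would be weak.** It would, and the protocol calls these p-values exploratory. That argues for paired descriptive counts, not for leaving the area out.

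Two further readings go too far. One is that causality is judged only against EHSG-KF. The causality item in 9.2 and the definitions in Table 9 are worded around the product, but 9.3.1 also covers study procedures, which include STSG grafting. The other is that the trial fails to show less donor-site morbidity. Section 8.1.1 states that those data are not collected, and no endpoint rests on them.

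**Conclusion.** The point holds as a contradiction within the protocol. Sections 6.3 and 10.3.3 promise a between-site comparison of AEs that 9.2, 9.2.1 and 10.3.8, as written, do not provide for. The effect is limited to local AEs without a per-area endpoint: mainly bleeding or haematoma, blistering, early pain or itch, granulation tissue and local serious events. For these the planned tables carry no information on the treatment difference. Systemic AEs cannot be assigned to an area under any plan, and the primary endpoint is unaffected.

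The conclusion assumes that the eCRF holds no mandatory location field beyond what 9.2 lists. If it does, the collection gap closes, and what remains is to align 10.3.8 with 6.3 and 10.3.3. With 12 to 15 patients the gain is a readable paired description of local safety, not a powered test.

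**What to change.** - **Section 9.2:** require a location for every AE: EHSG-KF area, control area, biopsy site, STSG donor site, or systemic/not attributable. The biopsy-site and donor-site categories keep those events out of the two study areas; no comparison between them is proposed.
- **Section 9.2.1:** record intermittent local AEs separately for each area.
- **Section 10.3.8:** tabulate local AEs and serious AEs by area with paired descriptive counts (EHSG-KF area only, control area only, both, neither). List unattributable events separately, as 10.3.5 does for infections.
- **Sections 6.3 and 10.3.3:** state that systemic AEs are reported per patient without comparison, as 10.3.10 does for quality of life and resource use.

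The cost is one eCRF field, retrospective coding of AEs already entered and one extra table. Some past events may have to be coded as not attributable where the source documents do not give a location; their number should be reported.

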### **9.2.1 Recording of Intermittent Adverse Events**

AEs which occur intermittently during treatment phase and are well known accompanying symptoms also from standard treatment for (large scale) skin defects like:

- Pruritus,
- Pain,
- Granulation tissue,
- Increased temperature/ fever (acute cases),
- Increased heart rate/ tachycardia (acute cases), or
- Nausea (acute cases)

are documented once as “intermittent” with start point (first manifestation) and endpoint (last occurrence of the symptom) in the eCRF. Assessment of causality is done also for all intermittent AEs.

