## 9.7 Anticipated Adverse Events

All complications that may be encountered during this study are AEs although they are, in all anticipated likelihood, not a direct consequence of the study product.

Rather, these complications or symptoms are well-known classical findings associated with any type of grafting of skin defects, namely infection, bleeding, unintended mechanical trauma (sheering forces acting upon fresh grafts) that may all lead to partial or complete graft loss. The management of these AEs encompasses additional dressing changes with wound cleansing/wound debridement (including vacuum-system-application), systemic and/or topical antibiotic therapy, and eventually re-grafting operations according to type and severity of the respective complication. In general, these complications are manageable in a straightforward way.

It is more difficult to envision AEs that are truly and solely arising from the use of EHSG-KF given the fact that all viable components are autologous and thus non-immunogenic, and all non-viable components (basically representing extracellular matrix components) have already been used in other clinical contexts without showing any significant AEs.

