## 10.3 Planned Analyses

### 10.3.1 Analysis Populations

Since randomization takes place during the operation procedure (or shortly before, as described in chapter 3.5), it is assumed that there is no difference between "randomized" and "treated" patients. Therefore, the following analysis populations are defined.

mITT (modified ITT) population: consists of all randomized/treated patients having at least 1 post-surgical measurement. The mITT population will be used for the analysis of efficacy variables, and statistical analysis will be done "as randomized".

PP (per protocol) population: consists of all patients adhering to the protocol. The PP population is subset of the mITT population. Subjects with major protocol deviations that might impact the primary endpoint will be excluded from this population. These deviations will be

determined before database lock. The PP population will be used for the analysis of efficacy variables, and statistical analysis will be done “as randomized”.

SAF (safety) population: includes all patients who have received a surgical treatment, irrespective of satisfying other criteria. This population will be used for the analysis of safety and tolerability, and statistical analysis will be done “as treated”.

The primary analysis will be performed using the mITT as primary analysis population, and PP as supportive. Secondary and exploratory efficacy analyses will only use the mITT. Safety analyses will be presented using the SAF.

Implications of administration of OOS products (see chapter 3.2.8) on analyses are expected to be minimal considering that only OOS products with a positive risk/benefit ratio on patient safety will be administered. Data of patients with OOS products administered are included in the analyses.

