### **10.3.10 Exploratory Analyses**

In addition to the primary endpoint and to the secondary endpoints, all exploratory endpoints listed in chapter 6.4 will be evaluated and tested for differences between interventional and standard treatment. The obtained p-values will be interpreted in a strictly exploratory fashion only, and no correction for multiple comparisons will therefore be applied. Statistical analyses for (secondary and exploratory) endpoints measured at multiple timepoints will focus on repeated measure models, to address the dependencies between visits. This will be a Generalized Estimating Equation model in case of binary data, and a mixed-effects model in case of continuous data. If data are not fulfilling underlying model assumptions, a transformation may be necessary before applying the statistical model. Details will be described in the SAP.

QOL assessments (EQ-5D and BSHS-B) and direct resource utilization cannot be used to compare interventional and standard treatment since these data are relevant at patient level and not at the site level. As a consequence, their analysis will be purely descriptive (without any p-value added).

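### Adverse events fall under a comparison of EHSG-KF with STSG sites (6.3, 10.3.3), but 10.3.8 and 9.2 do not carry the study area, so local events cannot be compared by treatment as written

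*Protocol*

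**What the plan says.** **The commitment.** Protocol 6.3 introduces its list of secondary endpoints with "Safety and efficacy evaluation, as a comparison between the EHSG-KF and control sites, based on"; adverse events from visit 2 onward are on that list. Section 2.3 places them under the same comparison with meshed STSG. Section 10.3.3 states that "all secondary endpoints listed in chapter 6.3 will be evaluated and tested for differences between interventional and standard treatment", with p-values read as exploratory.

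**The exemption.** Section 10.3.10 removes quality of life and resource use from the comparison "since these data are relevant at patient level and not at the site level". Adverse events are not named there.

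**The analysis.** Section 10.3.8 reads: "All adverse events will be listed by patient, phase (pre-treatment, treatment, post-treatment) and date of onset". It then summarises events in frequency tables for each phase, with optional tables for selected events such as serious ones. Section 10.3.1 assigns safety to the SAF population, analysed as treated: "This population will be used for the analysis of safety and tolerability".

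**The recording.** Under 9.2, "the information to be recorded in the source document and in the eCRF includes the nature of the AE, date and time of onset", followed by seriousness, severity, causality, duration, action and outcome. Under 9.2.1, six intermittent symptoms in the treatment phase, among them pruritus, pain and granulation tissue, are documented once, "with start point (first manifestation) and endpoint (last occurrence of the symptom) in the eCRF".

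**Infection.** Section 10.3.5 links infections to a site at visits 4 and 5. Section 10.3.13 applies the same approach at visit 6.

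**The concern.** In a parallel-group trial, an adverse event table by arm follows from knowing the patient's arm. Here both treatments are in the same patient, so the treatment is identified only by the area. The safety comparison therefore depends on an item that neither the adverse event analysis nor the named recording items mention.

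The complications that 9.7 anticipates are mostly events on a graft: "infection, bleeding, unintended mechanical trauma (sheering forces acting upon fresh grafts) that may all lead to partial or complete graft loss". These are the events for which a reader would want EHSG-KF set against STSG. If the area is not captured, a later SAP table by area would have nothing to draw on. The interim analysis in 10.1.3 may also use safety data, descriptively, in a request for a regulatory designation. A safety summary that cannot separate the two grafts would be weak there too.

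**Working it through.** The plan gives no figure on this point, so the check sets the sections side by side.

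1. **Is there a commitment to compare adverse events by treatment?** Yes. They are a 6.3 endpoint under the between-site heading, and 10.3.3 covers all 6.3 endpoints.

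2. **Is it withdrawn elsewhere?** No. Section 10.3.10 gives the right reason why patient-level data cannot compare the treatments, but applies it to quality of life and resource use only.

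3. **Does 10.3.8 deliver the comparison?** Not as written. The listing is ordered by patient, phase and onset date. The frequency tables are defined by phase, and their columns are not specified. The study area appears in neither.

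4. **Does the as-treated rule in 10.3.1 separate the treatments?** No. Each grafted patient has both treatments, so classifying the patient by treatment received leaves one group.

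5. **Do the recording rules secure the area?**
   - The items named in 9.2 do not include it. The wording is open-ended, so the eCRF may hold more.
   - Section 9.3.1 asks for relationship to the study procedure or the IMP, and Table 9 defines the categories against the IMP. Section 5.3 names the grafting of EHSG-KF and STSG as one procedure, and both grafts are placed in the same operation. A procedure-related rating therefore does not identify the area, and control-area events have no marker of their own.
   - Section 9.2.1 merges recurrences over time. It does not say what to do when both areas are affected.

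6. **What is already available by area?** Infection at visits 4, 5 and 6; graft take at visit 4; epithelialisation at visits 5 to 9; wound closure at visits 6 to 8; and POSAS, with patient-rated pain and itching, from visit 8. These would show the consequences of many local events. They do not count the events. Adverse events are collected to visit 12, three years after grafting.

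7. **Consequence.** If k patients have a local event on one area only, a count without the area reads k whether the number on the EHSG-KF side is 0, k or anything between. How large k would be cannot be derived from the protocol.

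**The case against.** The strongest reply is that this is a wording slip which the SAP can settle. In 10.3.8 only the listing is ordered by patient. Table columns are ordinary SAP content, and several neighbouring sections also leave the by-area comparison to 10.3.3, which refers to the SAP for details. The 6.3 heading cannot be meant literally for every event, since events count from visit 2, before any area is grafted. The same heading is repeated in the single-arm sub-study. Section 8.2.8 says only that events are evaluated and counted. With 12 to 15 patients, the listing can be read event by event.

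Much of this stands. The frequency tables are not fixed as patient-level tables, and systemic events cannot belong to an area. But a SAP table by area, or a reading of the listing, needs the area to have been recorded. The neighbouring endpoints are measured on each area by definition; adverse events are not.

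A reader might infer more than the text supports:
- *That the area is never recorded.* The list in 9.2 is open, an event term may name a location, and the eCRF is not shown.
- *That 9.2.1 makes both areas share one entry.* It is silent on this, and three of its six symptoms (fever, tachycardia, nausea) are systemic.
- *That infections outside visits 4 to 6 are lost in a measurable gap.* Visit 7 has photographs and adverse event, epithelialisation and closure assessments. Choosing visits 4 to 6 for scheduled infection assessment is a design choice, and the number of infections arising elsewhere is unknown and may be zero.

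**Conclusion.** The point holds as an internal mismatch. Sections 6.3 and 10.3.3 put adverse events under a comparison of the two sites, while 10.3.8 and the items named in 9.2 do not carry the area that the comparison needs. As written, local adverse events other than infections at visits 4 to 6 cannot be compared by treatment.

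Its size is qualitative. What suffers is the descriptive safety comparison of the two grafts. It might seem to follow that the trial's conclusion is at risk, but the documents do not support that: success rests on the primary endpoint alone, and secondary p-values are exploratory.

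The conclusion assumes that the eCRF does not already require the area. If it does, the data problem disappears and only the wording of 10.3.3 and 10.3.8 needs correcting. The sponsor should make the change, with medium confidence because the eCRF and SAP are not at hand.

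**What to change.** - **9.2:** require each local adverse event to be attributed to the experimental area, the control area, both, the donor or biopsy site, or neither/not attributable. The donor or biopsy site needs its own category because 1.3.1 claims lower donor-site morbidity as a benefit.
- **9.2.1:** clarify that an intermittent local symptom is entered once per affected area.
- **10.3.8:** summarise local adverse events, including site infections reported as adverse events, descriptively by area. Use the same fixed period after grafting for both areas. Keep systemic events at patient level.
- **10.3.3:** state that the adverse event comparison covers local events and is descriptive.
- **Patients already grafted:** query source records and the study photographs for the area. The protocol is version 12 of October 2022 and planned its first patient for early 2018, so this probably applies.

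Leave the infection endpoint at visits 4 and 5 unchanged. Do not let the counting period depend on whether an area is still open: healing is a post-treatment outcome, and the two areas of one patient could then be observed for different lengths of time.

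The cost is protocol wording, one eCRF field if it is absent, one descriptive table and a query round. Some past events may not be attributable. Attribution is open-label and partly retrospective, so the by-area counts should carry no test.
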